### Mali country context

Mali is, according to the Food and Agricultural Organization of the United Nations (FAO) definition, a Low-Income Food Deficit Country (LIFDC) with a population of 14 million people, over half of whom are under 15 years of age. According to the United Nations Development Programme (UNDP), Mali is ranked 178^th^ in the Human Development Index table, with an average life expectancy at birth of 48 years, adult literacy rate of 26 percent and a gross domestic product (GDP) per capita (PPP) of $1,083 USD. At a country level, Mali has seen remarkable progress in terms of access to school (net enrolment ratios increased from 20% in 1990 to 66% in 2007) but the levels of enrolment are still well below the average for Sub-Saharan Africa and completion rates are very poor^1^. A large proportion of children, girls in particular, are excluded from the schooling system. There are also large disparities within Mali; in the regions of Koulikoro and Mopti, for example, girls’ enrolment was estimated at 44% in 2005 [5].

Agricultural productivity in Mali is among the lowest in the world [6]. In Mali, the majority of farmers are involved in the production of food crops, with the main cereals being millet and sorghum. Production is carried out using a low level of technology: fertiliser use is minimal and access to credit is limited. Crop yields are not only low but also highly variable due to the fact that most farmers depend on rain-fed farming while rainfall fluctuates considerably from year to year and season to season [6].

According to the 2005 WFP food security and vulnerability analysis, an estimated 4 million people, or 40% of the population live in food insecurity or are highly vulnerable to food insecurity. According to this assessment, the regions most at risk are Kayes, Koulikoro, Mopti, Tombouctou, Gao and Kidal. The food security assessment also showed that food access is a primary constraint: food is available at markets when harvests are good but populations face constraints in food access and utilisation.

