## Design of the randomized evaluation

The national school feeding programme will be expanded in the regions of Mopti, Koulikoro and Kayes. These areas are among the most vulnerable of the country and offer a diversity of agro-climatic conditions and cropping patterns. Areas that are inaccessible for most of the year or in which there are serious security concerns were excluded from the study. The Ministry of Education has set clear criteria for the selection of the intervention areas. Priority is given to areas of food insecurity and vulnerability, poor enrolment rates (particularly of girls), poor presence of donors and of high community involvement. Similarly, criteria for the selection of schools include: schools with poor retention and completion rates (particularly of girls); schools with children from nomad and destitute families; schools with children with special needs; schools where one-third of class has to travel at least 3 km to reach the school; schools demanding canteens.

The impact evaluation is an integral component of the monitoring and evaluation activities of the national school feeding programme. The baseline survey is planned in intervention and control sites in 2012 and a follow-up is planned in 2014. By 2015 the control schools and community will be fully integrated in the intervention. We will consider the possibility of conducting further surveys in the following years building matched control groups in order to detect long term effects of the intervention on farmers’ productivity.

We discuss here two main elements of the evaluation approach: random assignment and manipulation of treatment; and threats to validity.

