Given the panel structure of the data there is a potential risk of differential attrition. However, it is difficult to predict why households or farmers from the control groups should respond to the interviews in different ways. Refusal to take part in the interview by households not benefiting from the project seems to be the main threat. However, as shown in the table above, the project has limited impact on household expectations in both project and control groups and, therefore, should have limited impact on response rates.

One issue with impact on cognitive development is that the observed impact can be the result of:

•Increased attention in school resulting from the energy meal (short term effect)

•Increased overall cognitive abilities resulting from protracted school feeding, school attendance, play time, social interactions …and so on… (long term effect)

A recent systematic review of school feeding interventions [26] observed that most evaluations have not been able to distinguish the two effects. This could be achieved through careful design of the intervention as the one shown in Table 5. Half of the project children are not given the meal on the day of the test until after the test, while half of the control children are given the meal before the test. The differences across columns (a-c and b-d) should produce the long term effect, while the differences across rows (a-b and c-d) should produce the short term effect. This approach will possibly be tested as a case study in a sub-sample of schools.

**Table 5 T5:** Teasing out short-term and long-term impact on cognitive development

	**Meal**	**No meal**
Project	a	b
Control	c	d

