## Methods of analysis

The analysis will follow the intention to treat approach as protocol and as treated, using econometric and simulation analysis, for all the relevant outcomes of the intervention. Impact will be assessed for the different treatment arms using regression analysis to account for potential confounding variables, using a “difference-in-difference” estimator.

As enrolment rates in Mali are very low in rural areas (around 30%), one problem in conducting this analysis is that school feeding may bring to school children of very poor backgrounds with poor nutritional status and cognitive abilities to start with. This problem can be overcome econometrically by controlling for such confounders during the data analysis.

A further difficulty of difference-in-difference analysis is serial correlation [28] resulting from unobserved factors affecting the outcomes that are themselves correlated over time and that produce auto-correlated errors and invalid standard errors. Serial correlation affects estimated standard errors and can lead to erroneous acceptance or rejection of null hypotheses but not the estimation of the effect size of the intervention. Thus, it may lead to erroneously finding or not finding a statistically significant impact of the intervention. See [29] for an illustration of how this problem can be addressed by calculating clustered standard errors, a procedure that is easily implemented using the Stata software. Clustered standard errors will also be employed in all cases in which correlated outcomes are observed within the same unit of analysis, for example, when the impact of the intervention is analysed at the school level and test scores within the school are obviously correlated. Similarly, clustered standard error will be used at the household level when the project is affecting more than one child within the same family as in the case of the impact on siblings that was discussed in Section Impact on nutrition.

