### Other general equilibrium effects

There is a possibility that some of the outcomes of the programme cannot be observed because of the type of intervention and the sampling design. In particular, the programme is likely to benefit only a few farmers in each of the project villages and the number of project villages for the study may not be sufficient to perform project-control comparisons that are statistically significant. In addition, there is a risk of large fluctuations within the trial period, which would tend to increase the variability in the outcomes and process measures – and, hence, possibly fatally undermine the power of the study due to this increased variability. We developed two strategies to mitigate this risk. The first involved the design of the study: we worked with Ministry of Agriculture technical stakeholders to spread the intervention area across a broad range of agro-ecological zones across the country. More importantly though, we devised an analysis strategy that includes two different simulations of the potential impact: The first is a micro-simulation of the farm-level impact of the intervention. Using household data we can estimate production and profit functions and then simulate the impact on farmers’ income, factoring in the additional demand and changes in food prices. Changes in prices can be simulated or observed directly through surveys. Similarly, the impact on consumption can be simulated after the estimation of a consumption function using household data. The second exercise consists of a village level simulation using a computable general equilibrium model. In this case, data are collected in one or two villages in order to build a social accounting matrix (SAM) to be used to simulate the impact of the injection of liquidity in the village economy. The advantage of this approach is that it allows the simulation of the impact on the entire community via price and demand effects. This method could also be used to simulate the differential impact of the programme in a drought and in a surplus year.

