### Income

No previous studies have investigated the impact of home-grown school feeding on farmers’ incomes and indeed this type of programme is entirely new. In addition, it is difficult to find programmes with effects similar to those of school feeding programmes. The Purchase for Progress programme by the World Food Programme, which similarly to the Malian school feeding programme purchases food for local producers, has modelled an increase in income by $50 dollars as a reasonable target for small African farmers. With a per capita GDP of $700 this corresponds to 7.5% of the average Malian income, though the income of small farmers is likely to be less than half the national average income. In addition, farm income is about 50% of total household income and the impact of a $50 increase on farm income is therefore much larger. We adopt 15% and 30% as minimum detectable effects of the programme on agricultural incomes of small farmers.

We adopt a conservative estimate of 10 farmers surveyed in each village, and based on data on agricultural incomes of Ghanaian farmers, we estimated the intra-class correlation coefficient (ϱ = 0.25) and the variance explained by site variability (B = 0.40). Note that given the high value of the standard deviation of income, similar in size to average income, the standardised difference and the percentage difference are almost equivalent. The probability of detecting an increase by 15% in agricultural income is 35% and the probability of detecting an impact of 30% is 88%. A power of 80% will be able to detect an income increase by 26%.

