### Conclusions

The power analysis suggests that the study will be able to detect an increase in enrolment by 5%, a 0.2 difference in test scores and an increase in farmers’ incomes by 25% between the school feeding interventions and the control group. The study will be able to detect changes in enrolment by 6%, differences in tests scores by 0.3 and changes in income by 40% between the regular school feeding and the HGSF+ components of the intervention see (Table 7).

**Table 7 T7:** Summary table of values used in the power calculations

	**Enrolment**	**Test scores**	**Agricultural income**
Alpha	0.05	0.05	0.05
N (observations)	55	25	10
J (schools)	2	2	2
K (clusters)	58	58	58
Intra Cluster Correlation	-	0.15	0.25
Between sites variability	-	0.20	0.40

While the sample size is well suited to the analysis of programme impact on attendance rates and test scores, it is clearly insufficient for the analysis of income effects of the HGSF+ intervention. However, we hope to overcome this problem in two ways: by increasing statistical power through restricted randomisation and by focussing on intermediate outcomes rather than on household income, a variable that has large variance and high within cluster correlation. First, in order to increase statistical power we will adopt ‘restricted randomisation’ [25]. We will use the baseline data collected at the village and school levels to remove the randomisation outcomes that would result in an unbalanced comparison of project and control communes. The randomisation of the HGSF+ component of the project within the 58 communes will be performed only within the restricted sample of balanced randomisation outcomes. Second, we will analyse intermediate indicators of household income such as input use (labour and other farm inputs, such as land, seeds and fertiliser) and farm capital use like animal traction, tools and simple machinery.

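### Difference-in-difference is the planned estimator; adjusting for the individual and village-mean baseline would be at least as precise, and the stated income power matches differencing only if the baseline-endline correlation is 0.5

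*Protocol article*

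**What the plan says.** Methods of analysis assesses impact for the treatment arms "using regression analysis to account for potential confounding variables, using a “difference-in-difference” estimator". The outcome's own baseline value is not named as a covariate. The section raises two difficulties: disadvantaged children being drawn into school, and serial correlation ("A further difficulty of difference-in-difference analysis is serial correlation"), which it handles with clustered standard errors. Neither concerns precision.

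There are two waves. Design of the randomized evaluation states: "The baseline survey is planned in intervention and control sites in 2012 and a follow-up is planned in 2014". Threats to validity treats the data as a panel: "Given the panel structure of the data there is a potential risk of differential attrition". Baseline values will therefore be available for the units followed up.

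For school feeding against control, the Income section of Appendix 1 gives 35% power at a 15% gain and 88% at a 30% gain, and states: "A power of 80% will be able to detect an income increase by 26" percent. For HGSF+ against regular feeding, the appendix gives 17% and 50% power at the same gains and 80% power at a 40% gain. Its Conclusions judge the sample too small for HGSF+ income effects. Table 7 lists alpha, sample sizes, intra-cluster correlation and between-site variability. It lists no correlation between waves.

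On volatility, Mali country context says "Crop yields are not only low but also highly variable", and Other general equilibrium effects warns that "there is a risk of large fluctuations within the trial period". Neither passage gives a figure.

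**The concern.** Randomisation already makes the arms comparable in expectation, so the baseline is not needed to remove bias; what it can add is precision. Differencing subtracts the whole baseline value, noise included. Regression on the baseline subtracts only as much as the data support. If the two waves are weakly correlated, differencing can be less precise than ignoring the baseline altogether.

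This matters most for farm income, a primary outcome. The plan itself doubts its power there and offers restricted randomisation, intermediate outcomes and simulation as remedies. Changing the estimator is not among them, although the baseline data are being collected anyway. In addition, the power that readers are shown belongs to a different analysis from the one planned.

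**Working it through.** **Inputs from the document.** Alpha is 0.05 (Table 7), taken as two-sided because sidedness is not stated. There are 58 communes, with 10 farmers per village, ICC ρ = 0.25 and site variability B = 0.40. The SD of income is about equal to its mean, so a 30% gain is about 0.30 SD. **Assumed input:** r, the baseline-endline correlation of income, which the document does not give; the range shown is 0.2 to 0.7.

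**1. Reproduce the stated power, HGSF+ against regular feeding.** The endline-only cluster formula is λ = J d² / (4[ρ + (1−ρ)/n]), with J = 58 and 56 degrees of freedom.
- The bracket is 0.25 + 0.75/10 = 0.325.
- d = 0.30: λ = 58 × 0.09 / 1.3 = 4.02, power 50.4% (stated 50%).
- d = 0.15: λ = 58 × 0.0225 / 1.3 = 1.00, power 16.6% (stated 17%).
- The effect detectable with 80% power is 42.7% (stated 40%, slightly optimistic).

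**2. Reproduce school feeding against control.** λ = K d² / (s² + 2[ρ(1−B) + (1−ρ)/n]), with K = 58, 57 degrees of freedom, and s² the variance of the effect between communes.
- s² = 0: the denominator is 2(0.15 + 0.075) = 0.45. Power is 38.8% and 91.7%, and the minimum detectable effect (MDES) is 25.1%.
- s² = 0.05, a value the document does not list: 35.5%, 88.8% and 26.5%, close to the stated 35%, 88% and 26%.

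Neither formula has a baseline or differencing term.

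**3. Compare the estimators.** With equal variances at the two waves, variance relative to endline-only is:
- difference-in-difference: 2(1−r)
- baseline-adjusted: 1−r²
- ratio, adjusted to differencing: (1−r²) / [2(1−r)] = (1+r)/2, which is below 1 for every r < 1.

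Differencing equals endline-only precision when 2(1−r) = 1, that is at r = 0.5.

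**4. Results over the assumed range.** Power in the first comparison uses λ from step 1 divided by the multiplier. MDES in the second is 26% times the square root of the multiplier; at r = 0.3, 26% × √1.4 = 31% and 26% × √0.91 = 25%.

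| r | HGSF+ vs regular, power at +30%: differencing / adjusted | School feeding vs control, MDES: differencing / adjusted |
|---|---|---|
| 0.2 | 34% / 52% | 33% / 25.5% |
| 0.3 | 38% / 54% | 31% / 25% |
| 0.5 | 50% / 62% | 26% / 22.5% |
| 0.7 | 72% / 79% | 20% / 19% |

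**5. Does the advantage survive clustering?** Suppose village-level r is 0.9 and farm-level r is 0.2 (assumed), with the variance components of step 1: village 0.25, mean of 10 farms 0.075, total 0.325.
- Differencing: [2(0.1)(0.25) + 2(0.8)(0.075)] / 0.325 = 0.17 / 0.325 = 0.52.
- Adjustment for the individual value only, one pooled slope b = 0.9 × 0.25 + 0.2 × 0.75 = 0.375: [(1 + 0.375²)(0.325) − 2(0.375)(0.24)] / 0.325 = 0.59, where 0.24 = 0.9 × 0.25 + 0.2 × 0.075 is the covariance of the village means across waves.
- Village-mean baseline included: the correlation of village means is 0.24 / 0.325 = 0.738, so 1 − 0.738² = 0.455.

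Individual-only adjustment can therefore lose to differencing. With the village mean included, the ratio is again (1+R)/2, where R is the correlation of village means.

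**The case against.** Difference-in-difference is unbiased under randomisation and sits within a covariate regression. The protocol contains no error of logic here, and a final data analysis plan is still to be approved by the independent steering group. All of that stands; this is a point about efficiency, not validity.

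A reader might infer more: that differencing fails to deliver the 26% detectable effect, or does worse than the appendix promises. The document does not support this, for three reasons.
- It gives no r. At r = 0.7 differencing beats both stated figures (20% against 26%; 72% against 50%).
- A large SD relative to the mean is spread between farms, not low correlation over time. Variable yields and rainfall make a low r plausible but do not measure it.
- The 26% belongs to a comparison of two villages in the same commune, where weather shocks shared across the commune cancel. They do not cancel in the between-commune HGSF+ comparison, so r may differ between the two. The comparison that the Conclusions of Appendix 1 call insufficient is HGSF+ against regular feeding, with its 40% figure.

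A reader might also infer that differencing can never be the more precise choice. Step 5 shows that it can be, if the regression adjusts only for the individual baseline. The recommendation therefore needs the village-mean term.

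The sentence on serial correlation concerns standard errors, which the plan handles by clustering. It is not itself at fault.

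**Conclusion.** The point holds as one of efficiency and of mismatch between power calculation and analysis. With the village-mean baseline included, adjustment is at least as precise as differencing at any correlation, apart from a degree or two of freedom out of about 56. The variance saving is (1−r)/2 when r is common to both levels: 40% at r = 0.2, 25% at r = 0.5 and 15% at r = 0.7. If variances differ between waves the ratio changes but not the direction, because regression estimates the slope that differencing fixes at 1.

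The stated income power describes the planned estimator only at r = 0.5. Below that the study has less power than stated under differencing, and above it more; the document does not settle which. The table assumes a common r at village and farm level and the appendix's 10 farmers per village. Its MDES column scales the whole stated 26%; any part of that figure due to effects varying between communes would not change with r, so the true spread would be slightly narrower.

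**What to change.** In Methods of analysis, make the primary estimator a regression of the endline outcome on:
- arm;
- the same individual's or farm's baseline value, with a missing-baseline indicator;
- the village-mean baseline;
- the design strata: commune for school feeding against control, and the variables used in the restricted randomisation for HGSF+ against regular feeding.

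Keep the clustered standard errors already planned, and retain difference-in-difference as a sensitivity analysis. In Appendix 1, say that the income figures are endline-only and give power for the chosen estimator over a range of r, separately for the two comparisons.

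The cost is analysis wording and a short recalculation, with no new data. At the protocol's status date the baseline survey was still under way and the endline was planned for 2014, so the change can be fixed before any endline outcome is seen.

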### Markets

We are not aware of studies of market integration in Mali. The Observatoire du Marche Agricole (OMA) collects agricultural prices on a weekly basis from more than 50 locations around the country. In principle, their data could be used to assess the extent of market integration, but not having access to the data we will assume in the following that markets are not fully integrated. If markets of staple foods (millet, sorghum and rice) are not fully integrated, prices can vary from one location to the other and the additional demand introduced by the project may have a positive impact on prices.

There are several markets of producer and consumer prices along the supply chain of staple foods. These markets are linked by complex relations and involve several actors: producers, collectors, bulkers, traders, retailers and consumers. The markets where the programme may have an impact are the *foire* (village, or group of villages, level market), the bulker market and the retailer markets. Foire markets in particular are markets where foods are purchased from local farmers by collectors and where local consumers make their purchases. If the project has an impact on prices it is likely to occur at this level. In practice, the impact on prices can happen a maximum of three times per year when purchases by the mayors are made and only in the HGSF+ programme sites.

Impact on prices could in principle be observed through the household level questionnaires. The farm gate price could be observed at the household level by including in the questionnaire questions related to prices paid and time of sales. This, however, would complicate the income section of the farmer questionnaire. Consumer prices are more difficult to observe in a standard household survey because the recall time is 7 or 30 days and there is only one survey per year.

As part of the programme monitoring activities, price data will be collected on a monthly basis for millet, sorghum and rice in the local foire next to each of the selected schools. The work could be assisted by the OMA through the provision of training given its long experience in the field. Collection of prices does not even require visits to markets if stable contacts can be established with collectors in each of the markets and prices could be communicated by phone.

